## Abstract

**Background:**

Combating the rise of drug-resistant organisms and minimizing side effects requires a shift in how we approach the duration of antibiotic therapy. A promising strategy involves tailoring the length of antibiotic therapy to patients’ needs, allowing discontinuation once patients feel better.

**Objective:**

This study aims to assess whether shortening antibiotic therapy based on patients’ recovery time is as effective as completing the full course in treating acute respiratory tract infections (RTIs).

**Methods:**

We plan to enroll a minimum of 474 outpatients ranging from 18 to 75 years of age with clinical features of acute RTIs across Spanish health centers. Patients diagnosed with acute lower RTIs or acute rhinosinusitis, deemed by clinicians to require a β-lactam course, will be randomized to either usual care, involving a full-course antibiotic therapy based on current guidelines, or a tailored approach. In the intervention group, patients will be advised to visit the center as soon as they feel better and are afebrile for a clinical assessment and C-reactive protein rapid testing. Treatment will be discontinued if these clinical results are normal. The primary outcome will be assessment of clinical resolution at day 14, while secondary outcomes include antibiotics given and duration; adherence to the prescribed antibiotic; other therapies given; early clinical assessment at day 7; days of severe, moderate, and any symptom, complications and reattendance within the first month; drug-related adverse events; absenteeism; and health-related quality of life. All participants will be given a symptom diary, recording their symptoms each evening. Additionally, a cost-effectiveness study and qualitative studies involving clinicians and patients aimed at exploring the strategy’s pros, cons, uptake, and satisfaction levels will be carried out.

**Results:**

The final results will be published by the end of 2027.

**Conclusions:**

We will examine whether adults who present with symptoms of RTI who are treated with antibiotic courses until they feel better are as effective as longer standard courses. It is highly important that a possible reduction in the antibiotic course as soon as the patient feels better does not compromise patients’ recovery. This comprehensive approach aims to shed light on the practicality and impact of tailoring antibiotic duration in RTIs.

**Trial Registration:**

ClinicalTrials.gov NCT06581367; https://clinicaltrials.gov/study/NCT06581367

**International Registered Report Identifier (IRRID):**

PRR1-10.2196/75453

## Introduction

The judicious use of antibiotics has played a vital role in saving millions of lives and preventing serious infectious complications. However, excessive and inappropriate antibiotic use has become a major contributor to the growing global crisis of antimicrobial resistance (AMR). Research has established a strong link between antibiotic consumption and the emergence of resistant bacteria, both at the societal and individual levels [1]. Given the limited pipeline for new antibiotic development, the responsible use of existing antibiotics, particularly in primary care, is crucial to contain AMR.

Primary care accounts for approximately 80% of all antibiotic prescriptions, with respiratory tract infections (RTIs) responsible for more than half of this total worldwide [2]. Inappropriate antibiotic use for uncomplicated RTIs remains widespread. Around 50% of general practice consultations for RTIs result in an antibiotic prescription, with large variations across practices (from 20% to 80%) [2]. In Spain, more than half of patients presenting with acute rhinosinusitis, acute bronchitis, or sore throat in primary care are treated with antibiotics [3]. This is concerning, as most uncomplicated RTIs in otherwise healthy adults are viral and self-limiting, and antibiotics offer no relevant benefit.

Despite numerous initiatives to curb unnecessary antibiotic use, the impact has been modest at best. While some local successes have been documented, most antimicrobial stewardship strategies have shown only minimal reductions in antibiotic prescribing [4]. For instance, a recent systematic review found that such programs reduce outpatient antibiotic use by just 4% on average [5]. As a result, general practitioners (GPs), who are potentially the most influential professionals in tackling the issue of AMR, continue to show a consistently high rate of inappropriate and unnecessary antibiotic prescriptions.

Traditionally, antibiotics have been prescribed for fixed durations—typically 7 to 10 days—regardless of individual patient response. However, accumulating evidence suggests that shorter courses are equally effective for many bacterial RTIs and result in fewer adverse events. The concept that “shorter is better” emerged over a decade ago and has since been supported by multiple clinical trials [6]. Except for conditions like tuberculosis and specific upper respiratory infections (eg, otitis media and streptococcal pharyngitis), shorter antibiotic courses have shown equivalent efficacy. For instance, 3-day β-lactam therapy is as effective as 8-day treatment in patients with community-acquired pneumonia who improve substantially by day 3 [7,8]. Similar findings have been replicated in acute chronic obstructive pulmonary disease (COPD) exacerbations [9] and suspected bacterial rhinosinusitis [10-12]. Even early trials of penicillin in pneumococcal pneumonia supported discontinuation after symptom resolution, with only 5% relapse [13].

Despite this, many guidelines continue to recommend longer treatment durations, often unsupported by robust evidence [14], and clinicians frequently default to 7-day prescriptions [15-17].

The notion that completing a full antibiotic course prevents resistance is deeply ingrained in medical training. However, this dogma is not evidence-based. In fact, prolonged exposure to antibiotics increases the selection pressure for resistant organisms, both in the patient and the environment [18,19]. Even short courses can have long-term ecological effects, including persistent colonization by resistant bacteria and disruption of the gut microbiota. Data indicate that beyond the first few days, the additional benefit of continuing antibiotics decreases, while the risk of harm, through side effects, superinfections, and resistance, increases [20-22]. Importantly, resistance tends to emerge not at the site of infection, but among colonizing flora elsewhere in the body [23]. Over the last years, there have been an increasing number of independent bodies, scientific academies, and institutions abandoning this dogma on completing antibiotic courses [24].

A promising strategy to reduce unnecessary antibiotic exposure involves tailoring treatment duration based on individual response. Conventional stewardship programs often fail to address overtreatment in patients who genuinely need antibiotics. Encouraging shorter, evidence-based durations may be a more practical and acceptable alternative, as shown in qualitative research [25]. The optimal antibiotic duration likely varies by individual. Factors such as age, comorbidities, immune status, bacterial load, and organ function influence how patients metabolize and respond to treatment [26,27]. A one-size-fits-all approach risks under- or overtreatment. For instance, in a landmark study, 3-day treatment was as effective as 8 days in 78.5% of patients hospitalized with mild to moderate pneumonia who had improved by day 3 [7]. It would not be unreasonable to think that the percentage of patients with pneumonia who feel better after 3 days of therapy would be even higher in primary care.

When a nonbacterial or self-limiting infection is suspected, the priority should be to avoid initiating antibiotics. For patients already on fixed-duration antibiotic courses, clinicians should consider advising discontinuation once symptoms are resolved, unless the infection is deemed potentially serious [25]. In such cases, reassessment with clinical examination or point-of-care tools like C-reactive protein (CRP) testing may be warranted before stopping treatment. Interestingly, one-third of patients already stop antibiotics on their own once they feel better. Studies using electronic monitoring show poor adherence to prescribed durations in real-world settings [28]. This emphasizes the need to align prescribing practices with patient behavior and current evidence.

Reducing antibiotic use in primary care remains challenging, particularly when faced with diagnostic uncertainty or patient expectations. Yet it appears more feasible to convince physicians to shorten therapy durations than to withhold antibiotics entirely, provided there is clear, high-quality evidence supporting this approach [29]. Emerging data from randomized trials suggest that most patients recover within 3 days, making shorter courses not only safe but preferable. Current stewardship strategies have only a limited impact, and a shift toward personalized treatment durations, based on clinical improvement and patient characteristics, offers a promising path forward [30]. Ultimately, we must transition from a disease-focused model to a patient-centered approach: we are not treating RTIs, we are treating patients with RTIs. To support this shift, we propose a pragmatic randomized clinical trial aimed at evaluating the effectiveness of individualized antibiotic duration in primary care. Such research could set a new standard for antimicrobial prescribing, reducing unnecessary exposure, preserving antibiotic efficacy, and promoting truly evidence-based care.

## Methods

### Study Design

This is the protocol for a pragmatic, randomized noninferiority trial with a two-group parallel design. The unit of randomization is the patient, and the allocation ratio between the control and intervention groups is 1:1. This protocol follows the SPIRIT (Standard Protocol Items: Recommendations for Interventional Trials) 2013 statement [31].

### Objectives

The primary aim of the STORM trial is to assess whether the clinical resolution on day 14 for adults presenting with symptoms of an acute lower RTI or acute rhinosinusitis in general practice is noninferior in the intervention group (stopping the antibiotic course as soon as patients feel better and clinical assessment is within the normal range) compared with the control group (patients completing standard antibiotic courses).

Secondary objectives of this trial are as follows:

Evaluate the antibiotic prescribed at the index visit and the planned and actual duration in the 2 groups.Evaluate the adherence to the prescribed antibiotic in the 2 groups.Evaluate the early clinical resolution on day 7.Evaluate the duration of symptoms in the 2 groups: (1) duration of severe symptoms, (2) duration of moderate symptoms, and (3) total resolution of symptoms.Evaluate the use of antibiotics other than the study medication and other symptomatic therapies within the first 4 weeks in the 2 groups.Determine the number of reattendances to any doctor regarding the infection within the first 4 weeks in the 2 groups.Determine the number of complications related to the infection within the first 4 weeks, such as visits to emergency departments, hospital admissions, in the 2 groups.Determine the number of adverse events in the 2 groups.Estimate the incremental cost per patient achieving clinical resolution (within-trial cost-effectiveness analysis) and the incremental cost per quality-adjusted life year (long-term cost-effectiveness analysis) in the 2 groups.Determine the number of days of work absenteeism due to the infectious disease in the 2 groups.Determine the improvement in health-related quality of life in the 2 groups.Assess the percentage of patients assigned to the intervention group who feel better and who comply with the criteria for stopping the antibiotic therapy in the 2 groups.

We hypothesize that patients with ages ranging from 18 to 75 years who are allocated to the intervention group and are asked to discontinue antibiotic therapy as soon as they feel better and afebrile, their clinical stability criteria are normal (systolic blood pressure >90 mm Hg, axillary temperature <37 °C, respiratory rate <20 breaths/minute, and oxygen saturation >92%) and CRP falls within normal range will have a similar overall clinical efficacy at day 14 and will not present a higher reconsultation rate compared with those allocated to the control group. We expect a lower number of drug-associated adverse events in the intervention group.

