### Interventions

Patients assigned to usual care will be given a full course of the first-line antibiotic course as recommended by the updated local guidelines [34,35]: amoxicillin 750 mg 3 times daily (t.i.d.) for 7 days for acute rhinosinusitis, 1000 mg t.i.d. for 7 days for suspected pneumonia (with clavulanate if the patient is older than 65 years), and amoxicillin/clavulanate 875 mg/125 mg t.i.d. for 7 days for suspected acute exacerbations of COPD (Table 1). Nonetheless, this guideline is designed to serve as a reference for making informed and improved choices in prescribing. The decision to prescribe an antibiotic is solely at the discretion of the participating doctor. The trial is pragmatic, thus mirroring the real-life practices of doctors in Spain. Doctors may also prescribe antibiotics for longer regimens, such as 10-day durations, as shown in recent studies [36]. The decision to prescribe an antibiotic will always be made before randomizing the patient.

Patients in the intervention group will be treated accordingly, following the same recommendations as patients assigned to the control group, but they will be asked to return as soon as they feel better and are afebrile.

When deciding whether to discontinue the antibiotic course after a patient feels better during a consultation, the participating professionals must assess three key areas:

Overall improvement in the patient’s symptoms.Evaluate the vital signs, confirming that most of them are within the normal range and that the following clinical criteria are met: temperature <37 °C, blood pressure >90/60 mm Hg, pulse <100 beats/min, respiratory rate <20 breaths/min, and oxygen saturation >92%.Assess the CRP value and interpret the results according to the provided table based on current recommendations [37].

Patients who meet all these criteria will be asked to discontinue treatment. Otherwise, patients will be instructed to continue the course for 2 more days and, if they continue feeling better, to return for reassessment. In case of worsening symptoms, they will be advised to contact their doctor for clinical assessment. The doctor will then decide whether to recommend completing the full antibiotic course, changing the therapy, or making a referral.

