
#### Sample Size

We assumed 85% clinical recovery in the group assigned to the full antibiotic course based on some studies [12,42-44]. Considering a power of 80%, a level of significance of 5%, one-sided noninferiority margin of 10%, as recommended by the guideline on the evaluation of medicinal products indicated for treatment of bacterial infections issued by the European Medicines Agency in 2022 [45], which gave a sample size of 402 patients. Assuming that the primary outcome could not be evaluated in 15% of patients, 474 patients needed to be included in the study (237 in the control group and 237 in the intervention group).

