### Statistical Methods

Statistical methods for primary and secondary outcomes: The characteristics of the study population will be described using frequencies for categorical variables and mean and SD for quantitative variables. To compare the clinical efficacy between the 2 strategies, we will analyze the difference in the proportion of recovered patients in each arm on day 14. Efficacy evaluation will be primarily based on intention-to-treat analysis in such a way that any event in any patient will be included in the group to which the patient was randomized, and per protocol analysis will be used as a secondary analysis. For all analyses, the level of significance will be *P*<.05.

Interim analyses: No interim analysis is planned.Methods for additional analyses (eg, subgroup analyses): We will conduct subgroup analyses of the primary outcome of participants with lower RTIs, and for acute rhinosinusitis.

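### The planned conclusion is about shorter courses, but the hypothesis and primary analysis do not require that courses were in fact shorter

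*Protocol article*

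**What the plan says.** Study Design describes a "pragmatic, randomized noninferiority trial with a two-group parallel design". The hypothesis at the end of Objectives is that intervention patients "will have a similar overall clinical efficacy at day 14 and will not present a higher reconsultation rate", followed by one directional expectation: "We expect a lower number of drug-associated adverse events in the intervention group". Antibiotic exposure does not appear in it.

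Statistical Methods rests the efficacy comparison on day-14 resolution: "we will analyze the difference in the proportion of recovered patients in each arm on day 14". Intention to treat is primary and per protocol is secondary. Sample Size takes the 10-point margin from a European regulatory guideline.

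Planned and actual antibiotic duration is the first secondary objective, to be evaluated, and is listed among the diary outcomes as a mean or median. The share of intervention patients who feel better and meet the stopping criteria is under Other Outcomes. Neither has a hypothesis, a target difference or a role in the conclusion.

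The Conclusions paragraph of the abstract says the trial will examine whether adults "treated with antibiotic courses until they feel better are as effective as longer standard courses". The abstract's Objective is also framed as shortening therapy versus completing the full course.

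**The concern.** A noninferiority result supports a statement about shorter treatment only to the extent that treatment was shorter. Under this protocol an intervention patient can follow every instruction and still take antibiotics for a full course or close to it. Those who do not meet all stopping criteria continue: "Otherwise, patients will be instructed to continue the course for 2 more days", with a return for reassessment if they still feel better. Table 2 rules out stopping when CRP is above 100 mg/L, and for COPD patients at 40-100 mg/L. Stopping also depends on the patient coming back. The Introduction adds that one-third of patients already stop on their own once they feel better, which would narrow the contrast from the control side.

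If the arms end up treated much alike, the day-14 difference is a diluted version of any effect of stopping early. The trial could then meet its margin and be read as evidence on shorter courses that it does not provide. The per-protocol analysis does not resolve this, because continuing after failing the criteria is itself per protocol.

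**Working it through.** **Inputs from the protocol.** "We assumed 85% clinical recovery in the group assigned to the full antibiotic course"; "the allocation ratio between the control and intervention groups is 1:1"; margin 10 points; power 80%; 402 evaluable patients, 474 after allowing for 15% not evaluable.

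**Reproducing the sample size.** n per arm = (1.960 + 0.842)² × 2 × 0.85 × 0.15 / 0.10² = 200.1, rounded up to 201, so 402. Then 201 / 0.85 = 236.5, rounded up to 237, so 474. This is a one-sided 2.5% test; one-sided 5% would give 158 per arm. One-sided 2.5% is used below.

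**Inputs not in the protocol (assumptions).** s, the share of intervention patients who stop early, is taken from 0% to 100%. h, the loss of day-14 resolution among those who stop, is taken as 10, 15 or 20 points. All control patients are assumed to complete their course.

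**Chance of declaring noninferiority.** Let d = s × h and the intervention rate = 0.85 − d. With 201 per arm, SE = √[(0.85 × 0.15 + (0.85 − d)(0.15 + d)) / 201], and the chance = Φ((0.10 − d)/SE − 1.96).

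Example with s = 20% and h = 15 points: d = 0.03; SE = √[(0.1275 + 0.1476)/201] = 0.0370; (0.07/0.0370) − 1.96 = −0.07; chance 47.3%.

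| Share stopping early | h = 10 | h = 15 | h = 20 |
|---|---|---|---|
| 100% | 2.5% | 0.1% | <0.1% |
| 75% | 9.4% | 1.2% | 0.1% |
| 50% | 26.2% | 9.4% | 2.5% |
| 25% | 53.2% | 38.8% | 26.2% |
| 10% | 70.3% | 64.8% | 59.0% |
| 0% | 80.2% | 80.2% | 80.2% |

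With h = 0 the chance is 80.2% at every share.

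**What a superiority test on antibiotic days would add.** With 201 per arm, two-sided 5% and an assumed SD of 2 to 3 days, power for a 1-day mean reduction is 99.9% (SD 2), 98.0% (SD 2.5) or 91.6% (SD 3). Now assume those who stop save 4 days each:

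- 10% stopping: mean reduction 0.4 days. The standard error is SD × √(2/201), which is 0.200 (SD 2) or 0.299 (SD 3). Power = Φ(0.4/SE − 1.96), about 52% (SD 2) or 27% (SD 3).
- 20% stopping: mean reduction 0.8 days. Power is about 98% (SD 2) or 76% (SD 3).

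The test therefore guards mainly against very low early stopping.

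**The case against.** The strongest reply is that the trial compares strategies. Objectives defines the intervention as stopping when the patient feels better and the assessment is normal, so continuing on a high CRP is part of the strategy and not failed delivery. This stands. With h = 15 points and 10% to 50% stopping, the true difference between arms is 1.5 to 7.5 points, inside the margin, so noninferiority is the correct decision about the strategy. A reader might infer that a harmful strategy slips through by error; the documents do not support that.

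Three other stronger readings also fail:

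- That low uptake always gives the best chance of success. This holds only if stopping does harm, and the protocol gives no reason to assume 15 points.
- That the 10-point margin was accepted in exchange for less exposure. Sample Size cites a regulatory guideline instead.
- That every patient who fails the criteria finishes the full course. Interventions allows reassessment after 2 days and stopping then.

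Low uptake is also not a given. The Introduction cites 78.5% of hospitalised pneumonia patients improved by day 3 and expects more in primary care. That is improvement, not stopping, but it makes shares above 50% relevant. The day-3 reminder call, the dedicated phone at each centre and the preference for centres with Saturday or out-of-hours opening all support separation. Duration is measured in both arms and checked against records, so readers could see poor separation.

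Finally, ranking secondary outcomes is often left to a statistical analysis plan, which is not shown. The point therefore rests on the hypothesis and the planned conclusion, both stated here and not aligned.

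**Conclusion.** The mismatch holds: a conclusion about shorter courses is planned, while the stated hypothesis and primary analysis can be satisfied whether or not exposure fell. The primary analysis itself is not wrong. If stopping carries some harm, dilution moves the chance of noninferiority from 9% at 50% stopping to 65% at 10% (h = 15 points, 201 per arm), against 80% when nobody stops. In the low-stopping cases the result is sound for the strategy and weak for shorter courses. The shares, losses, days saved and SDs are assumptions, because the protocol gives none. This is a matter to correct in the wording of the hypothesis, analysis and conclusion before the data are analysed; it does not threaten the design.

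**What to change.** 1. In Objectives (hypothesis) and Statistical Methods, name total antibiotic days as the key secondary outcome, tested for superiority at the same level only after noninferiority is shown (fixed sequence).
2. Count antibiotic days in both arms to the end of treatment. The diary section now ends its calculations at day 14 or once every symptom scores 0, whichever is earlier. Read literally, that would drop control-arm days taken after recovery, which are the days the intervention aims to save.
3. Beside the primary result, report the percentage of all randomised intervention patients who stopped before their planned end date, with its confidence interval. The existing outcome counts those who feel better and meet the criteria, which is not the same thing.
4. Conclude that shorter courses are as effective only if both tests are met. Otherwise limit the conclusion to the strategy as delivered and state that a reduction in exposure was not demonstrated. Do not state that shortening was untested, since a nonsignificant difference in days does not show that.

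Cost: wording only. Antibiotic use is already collected through diaries, the day-14 call and medical records, and the fixed sequence needs no alpha split and no extra patients. The downside is that the claim about shorter courses becomes slightly harder to make. Because the superiority test does little once 20% or more stop early, the reported percentage has to carry the rest of the interpretation.
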